#### Plans to promote participant retention and complete follow-up

The patients will receive extensive information about the study set-up and requirements during the recruitment. The importance of completion of the follow-up will be stressed. Patients are allowed to stop at any time during the study and are not obliged to give a reason to discontinue. If possible, the patient will be asked to complete the survey at 2, 4 and 6 months after inclusion. Questionnaires are completed using the mobile app, and therefore participants can do this at any convenient moment. All patients are reminded throughout mobile app notifications to fill out the questionnaires. Throughout the follow-up period, the researchers will check responses and if necessary, contact participants for completion of their follow-up.

#### Data management

Data collected through the app will be entered in a private dataset hosted on a secure university-based server. Two independent researchers will perform the analysis to control for potential errors.

#### Statistical methods for primary and secondary outcomes

Normality of the variables will be detected by Kolmogorov–Smirnov test. A series of repeated measures ANCOVAs will be performed to assess the effectiveness of the smartphone app on the outcomes. The baseline scores on the scales will be entered in the statistical model as covariates, the type of target group as a factor and the scores for each timepoint as dependent variables, respectively. Effect sizes will be calculated as Squared Eta indices (η^2^) according to the formula provided by Olejnik and Algina (2003). Following Cohen et al. (1998), effect sizes of 0.01, 0.06, and 0.14 will be interpreted as small, medium, and large, respectively. The statistical significance will be set at *p* < 0.05.

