### Outcomes

The effectiveness of the mobile app will be evaluated on the following outcomes: (i) perceived susceptibility and severity of the pandemic situation, perceived benefits, and costs of preventive health behavior’s (such as using a mask), (ii) knowledge about Covid-19 preventive behavior’s and negative consequences of social distancing, (iii) stress and psychopathological symptoms (i.e., anxiety, depression, and post-traumatic stress symptoms) and cognitive distortions.

These variables will be measured at a baseline assessment (i.e., each participant will complete the questionnaires within 2 weeks before using the app), at an intermediate evaluation (i.e., 2 months after the baseline evaluation), at a post-test evaluation (i.e., 4 months after the baseline evaluation), and at a follow-up evaluation conducted 6 months after the baseline assessment. The endpoint consists of the variation in depressive, anxious and stress states, cognitive distortions, and coping strategies, from the baseline to the intermediate, post-test and follow-up evaluations. The scores in all questionnaires that measure the endpoints will be aggregated in the form of mean scores with relative standard deviations at every evaluation. No harm derived by the use of the self-help application is expected.

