#### Sample size

According to an *a-priori* power analysis, at least 1,800 participants are required to conduct a repeated measures ANCOVA with between-within factors and interactions to estimate a medium effect size on each one of the outcomes with 95% power and a significance level set at 0.05.

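### No outcome, visit or model effect is named as deciding, so the stated 0.05 does not hold for a claim that the app is effective across at least nine scales

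*Protocol article*

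**What the plan says.** All references are to the protocol article.

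- **Analysis.** The section headed "Statistical methods for primary and secondary outcomes" plans that "A series of repeated measures ANCOVAs will be performed to assess the effectiveness of the smartphone app on the outcomes". On the threshold it says "The statistical significance will be set at" p < 0.05. It names no primary outcome and no adjustment for the number of tests.
- **Endpoint.** *Outcomes* says: "The endpoint consists of the variation in depressive, anxious and stress states, cognitive distortions, and coping strategies, from the baseline". The later evaluations are at 2, 4 and 6 months. None of these components or visits is ranked above another. The outcome list just before that sentence does not match it. Coping appears only in the endpoint sentence, while post-traumatic stress symptoms and knowledge appear only in the list.
- **Scales.** *Plans for assessment and collection of outcomes* gives DASS-21 (stress, anxiety, depression), the Cognitive Distortions Scale (one factor in the Italian version) and COPE-NVI-25 (five subscales). A health-belief questionnaire is set apart as an additional endpoint.
- **Power.** *Sample size* names the model as "a repeated measures ANCOVA with between-within factors and interactions". The purpose of the calculation is given as "to estimate a medium effect size on each one of the outcomes", and its error rates are stated in the phrase "with 95% power and a significance level set at 0.05".

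**The concern.** The heading promises a distinction that the text never makes. The article says what will be measured and at which level each analysis is tested, but not which result would answer the question of effectiveness. The 0.05 in *Sample size* and in the analysis section controls the error of one test. The conclusion that the app is effective would be drawn from a series of tests, and nothing limits the error of that conclusion to 5%.

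This is not a detail that can wait for an analysis plan. An adjustment method might be left to one, but naming the primary outcome belongs in the protocol. Here the protocol fixes a bundled endpoint and a single threshold for the whole series. At stake is whether the trial has a defined confirmatory test at all.

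**Working it through.** **The plan's own figures.** The only error rate stated is 0.05 per test, so there is no family-wise figure to reproduce. The sample size ("at least 1,800 participants are required") was tried with a medium effect of f = 0.25 (η² about 0.06), 95% power, 4 or 5 groups, 3 or 4 measurements and assumed correlations of 0, 0.5 and 0.8. The variants gave about 16 to 425 participants. Inflating the largest for 48% dropout gives 425 / 0.52, or about 818. The figure of 1,800 is not reproduced. That is a separate matter, and nothing below depends on it.

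**Step 1: number of scales.** DASS-21 3 + Cognitive Distortions Scale 1 + COPE-NVI-25 5 = 9. The count is 10 if the two cognitive distortion domains are scored separately, and higher with the health-belief scores, whose number is not given.

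**Step 2: one time-effect test per scale, independent.** The chance of at least one false positive among m tests is 1 − 0.95^m.

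- m = 9: 1 − 0.95^9 = 0.370
- m = 10: 1 − 0.95^10 = 0.401

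**Step 3: the same nine tests, correlated.** Scales answered by the same people are correlated, but the documents give no correlations, so those below are assumptions. Two simulations were run. One used equicorrelated normal statistics (200,000 draws). The other used chi-square time effects (40,000 draws) with 5 groups and 3 measurements, or 4 groups and 4 measurements.

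| Between-scale correlation | Normal statistics | Time effect, 5 groups × 3 | Time effect, 4 groups × 4 |
|---|---|---|---|
| 0.3 | 0.325 | 0.332 | 0.334 |
| 0.5 | 0.269 | 0.270 | 0.281 |
| 0.7 | 0.201 | 0.209 | 0.213 |
| 0.9 | not run | 0.124 | 0.129 |

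This is about 20% to 33% for correlations of 0.7 to 0.3, and about 12% at 0.9.

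**Step 4: every change in the endpoint sentence.** Nine scales × three changes from baseline = 27 tests (60,000 draws; both correlations assumed).

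| Between-scale correlation | Within-scale 0.5 | Within-scale 0.7 |
|---|---|---|
| 0 | 0.702 | 0.644 |
| 0.3 | 0.644 | 0.589 |
| 0.5 | 0.556 | 0.501 |
| 0.7 | 0.444 | 0.391 |

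This is roughly 40% to 70%.

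**Step 5: what control would cost in power.** Bonferroni over 27 tests is 0.05 / 27 = 0.00185 per test. For the plan's medium effect, 95% power at that level needs at most 650 participants in the variants run at correlation 0.5. With 1,800 × (1 − 0.48) = 936 left after 48% dropout, power stays above 99%. Holm over eight secondary scales starts at 0.05 / 8 = 0.00625, which is less strict, so it needs no more participants.

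**The case against.** **The error is not shown to be likely.** A reader might infer that a false claim of effectiveness is more likely than not. One could count time, group and group-by-time effects on nine scales as 27 tests and quote 1 − 0.95^27 = 0.75, or about 0.52 to 0.70 at between-scale correlations of 0.7 to 0.3. The documents do not support this as the headline. The three effects are inferred from the wording in *Sample size*, and the analysis section does not list them. A group main effect says that the populations differ, not that the app works. *Objectives* already describes differences between populations as something to be explored. For the nine time-effect tests the figure stays below one half. This objection stands, and the 75% should not be used.

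**No rule says that any significant result means success.** A reader might also infer that one significant scale or visit would be declared proof. The article states no such rule, specifies no visit-by-visit contrasts and asks for effect sizes with interpretive thresholds alongside p-values. That is fair. But it states no other rule either, and it defines the endpoint as changes to three visits, so the 27-change count in the working is conditional on those changes each being tested.

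**Some ordering exists.** The health-belief questionnaire is called an additional endpoint, although the outcome list puts the same beliefs first. Nothing is ranked among the nine scales, so this does not answer the point.

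**A named primary would not make the trial confirmatory of an app effect.** This stands. *Trial design* describes a single group with no control. Natural recovery or regression to the mean could make one pre-specified scale significant.

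**Conclusion.** The point holds in this form: no outcome, visit or effect is named as deciding, and the stated 0.05 does not apply to a claim of effectiveness drawn from the series.

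The size depends on which tests decide, which the article leaves open. With nine time-effect tests it is 37% under independence, about 20% to 33% at correlations of 0.7 to 0.3, and about 12% at 0.9. With 27 changes from baseline it is roughly 40% to 70%. Even the lowest figure is more than twice 5%. All these figures assume no true change on any scale. The correlations are assumptions, and the health-belief scores are left out of the count.

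The conclusion concerns the nominal error rate only. It does not show that a false claim is probable, and curing it would not rule one out in an uncontrolled trial.

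**What to change.** Before enrolment:

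1. Name one primary outcome, visit and deciding effect. One choice that fits the aim of stress self-management is the change in DASS-21 stress from baseline to the 4-month post-test, at two-sided 0.05. The documents do not dictate this choice; what matters is that a single one is fixed. State the test as that contrast, because a general time effect does not say which visits differ.
2. Make the other eight scales at 4 months secondary, with Holm adjustment (smallest p-value against 0.05 / 8 = 0.00625). State whether they are tested only if the primary succeeds. If they are not, 5% holds within each family but not across both.
3. Report the 2- and 6-month contrasts, the health-belief items and the group and group-by-time effects as exploratory, with confidence intervals.
4. State that a significant primary result shows change over time and does not by itself attribute that change to the app.

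The cost is wording, plus formal notice to the ethics committee, which *Ethics and dissemination* requires for any protocol change. Fewer results can be called significant. No extra participants are needed for the plan's medium effect.

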#### Methods in analysis to handle protocol non-adherence and any statistical methods to handle missing data

Missing baseline data will be treated by multiple imputation (Sinharay et al., 2001). Missing longitudinal data will be managed through an intention-to-treat analysis with the last observation carried forward technique (Newell, 1992). The statistical analyses will be carried out by the software SPSS version 25.00.

### Monitoring

#### Composition of the coordinating center and trial steering committee

This is a multicenter study designed and coordinated in the Department of Medical Sciences, Surgery and Neurosciences, University of Siena. Day to day support for the trial is provided by:

Principle investigator: takes supervision of the trial. Data managers: organizes data capture, safeguards quality and data. Study coordinators: coordinates study phases, annual safety reports.

The study team meets every month to monitor the study progress and the potential pitfalls. There is no trial steering committee or stakeholder and public involvement group. The decision to terminate the study is up to the principal investigator.

#### Adverse event reporting and harms

All adverse events reported by the subject will be recorded and handled by the principal investigator.

#### Auditing

The Ethical Committee of the “Azienda Ospedaliera Universitaria Senese” will independently carry out interim and final monitoring of the study. The Funding Body, that is the Tuscany Region, has carried out (i) a first mid-term audit of the progress of the works with respect to the schedule and the milestones achieved, (ii) a financial statement on the reporting of expenses, and (iii) a special interim report on the activities carried out 1 year after the start of the project. A final verification by the Region on the same parameters will be made at the end of the project.

## Ethics and dissemination

The research protocol of this study was approved by the Ethical Committee of the “Azienda Ospedaliera Universitaria Senese” (Italy) on 28th October 2021 (Approval code: 20831). The Ethical Committee will be formally informed of any changes to the protocol. According to Wies et al. (2021), digital health technologies provide technical, scientific, ethical, and regulatory challenges. Despite the centrality of data collection for study purposes and for the administration of the platform, the users’ privacy and security need to be assured, so all the private information will be anonymous. Participants will be informed of the data management policy and anonymity will be guaranteed before obtaining informed consent.

### Dissemination policy

The study results will be published in a peer-reviewed journal regardless of the result. Additionally, participation and presentations at relevant national and international academic conventions will promote dissemination. Patients will receive a summary of the results in case they opted-in to receive outcomes on a study level.

## Anticipated results

The results of this study will provide helpful knowledge and insights into the effects of using an app for self-monitoring and managing long-term stress symptoms during pandemic periods. Self-management methods can be a resource to enable people to deal with stressful events, to discover external/internal resources, to mobilize them and to promote effective coping strategies in a health-promoting manner. Indeed, supporting people’s involvement in their care to identify problems early, also promotes more timely initiation of necessary treatment. Data obtained from the small pilot sample of users through direct observation, data collection through the application, and questionnaire administration will be triangulated to enhance the next application version. More specifically, the repeated measures from the baseline assessment to the follow-up evaluation will allow to identify potential critical points that might need to be improved or modified in the following app implementation. Furthermore, users’ responses to written and audio-visual psychoeducation materials usage, ABC diaries, cognitive restructuring and problem-solving cards, meditation and distancing from automatic thoughts exercises, and factsheets on the construction of personal values will provide useful information for the final app improvement. Moreover, these contents might help users to self-manage and self-monitor not just COVID-19-related stress, but stress in general and psychological long-term consequences, such as depression and anxiety. For example, the ABC diary used to face specific pandemic-related situations could be employed also in everyday life stressful conditions.

Our study samples will be large and heterogenous and will include subjects with different ages: from young adults over 18 years to elderly individuals. So, the mobile platform for stress-self management will not be restricted for use and application with the target vulnerable populations, but it can also be transferred to other populations and contexts. If successful, we anticipate the platform could have clinical benefits to various groups by providing symptom monitoring and early intervention and decreasing barriers to treatment-seeking. In fact, the population-level approach has the potential to improve mental health outcomes in pandemic periods for many people. If this protocol is proven effective, it can be expanded to any population at risk of experiencing mental distress during a continuous public health emergency such as the Covid-19 pandemic.

Moreover, if effective, this application could also be implemented in other similar contexts in which stress management could be particularly helpful like in the business and school sectors. Non-healthcare workers, high school students, and teachers present similar characteristics to those of our population and could benefit from an app targeting.

Although the current protocol is addressed solely to Italian-speaking individuals, a future potential expansion could involve the integration of facilitators to reach underserved people from other ethnic groups.

### Trial status

The current protocol is version 1 of 04-11-2022. It is estimated that patient recruitment will begin in February 2023 and will be completed around September 2023. Currently, we are approaching the pilot phase of the study that will begin in December 2022.

## Ethics statement

The studies involving human participants were reviewed and approved by Ethical Committee of the University Hospital of Siena. Approval code: 20831. The patients/participants provided their written informed consent to participate in this study.

